## Potential Risks and Benefits

### Potential Risks

No potential risks have been identified in preclinical studies of the investigational vaccine candidate in the course of the animal work performed using different vaccine formulations. However, due to the fact that the J8 peptide is part of the M-protein, there exists the potential of inducing local and systemic reactions as reported in other studies that involved investigational group A streptococcus vaccines based on the M protein. These include local reactions such as mild to moderate erythema accompanied by swelling and tenderness at the injection site. Another possible risk is the induction of a human cross reactive (autoimmune) antibody response of a similar quality that may lead to the pathology observed in RHD and RF in the study participants. However, safety monitoring will be included throughout the study. Serum screening using rabbits for cross reactive antibodies in the vaccinated participants in GAS vaccine studies has been reported previously [13]. However it has been shown that this assay is limited in demonstrating the safety of the vaccine in respect to induction of cross reactive antibodies. At present, there is no sufficiently well developed and reliable assay that could be found in non-human primates [37-43], thus serum samples will be kept for each participant at time points indicated in this protocol and tested should better assay become available.

Possible risks could also include allergic reaction to the vaccine components or reactions reported with the administration of vaccines containing diphtheria toxoid conjugate in their composition.

These reactions include headache, localized pain, redness and swelling at injection site, fever, fatigue, anorexia, diarrhea and less commonly reported reactions such as vomiting and rash.

Other possible risks would also include the risks associated with the process of obtaining clinical samples e.g. (blood) i.e. venipuncture. These risks would include mild discomfort due to venipuncture, swelling, bleeding at the site of venipuncture, and bruising at the puncture site. Light headedness/fainting could also occur at the time of the blood collection, but this is uncommon and on rare occasions, infections due to the venipuncture. In accordance to the clinical site procedures, standard precautions will be taken to reduce the likelihood of these difficulties.

### Known Potential Benefits

There are no known direct benefits to the participants receiving the Group A streptococcus vaccine. There will be benefit to the community by contributing to research for the development a group A streptococcus vaccine. There may be a benefit to the participant from the results of the screening tests and procedures (blood tests, electrocardiogram (ECG) and transthoracic echocardiograms (ECHO)).

# Objectives

## Study Objectives

**Primary objectives:**

To evaluate the safety of a Group A streptococcus vaccine candidate delivered intramuscularly to healthy adults in two doses of 50 µg of AcJ8-D adsorbed onto alum.

**Secondary objective:**

To assess the immunogenicity of a Group A streptococcus vaccine candidate delivered intramuscularly to healthy adults in two doses of 50 µg AcJ8-D adsorbed onto alum.

## Study Outcome Measures

### Primary Outcome Measures

The safety of the vaccine candidate will be assessed on the basis of the frequency and occurrence of injection site and systemic reactions following administration of the investigational vaccine. Adverse events (AE) and serious adverse events (SAE) will be reported throughout the duration of the study. Safety parameters that will be monitored include changes in physical examination including cardiac auscultation, clinical biochemistry and hematology testing on blood and urine, and changes in electrocardiogram or transthoracic echocardiograms.

### Secondary Outcome Measures

• The production and the titer of the vaccine specific antibodies of the baseline titer after study product administration will be determined using ELISA. The presence of vaccine-specific antibodies in all participants in the study will be monitored and the titer of the vaccine specific antibodies after each dose of the vaccine candidate will be measured to investigate the relationship between the doses administered and the titer of vaccine-specific antibodies.

• The bactericidal activity of the induced antibodies against different standard reference strains of group A streptococcus such as M1, M6 and 88/30 (Australian clinical isolate) will also be assessed.

# Study Design

This study is a double blinded, randomized Phase I single cohort clinical study (N = 20 participants). The participants will be randomized 3:1 to receive the intervention (N=15) or control (saline), (N=5). Each participant will receive a total of two injections with an 8-week interval between injections.

To investigate for the occurrence of any immediate serious adverse reactions to the injected vaccine candidate, two (2) participants (one randomized to receive the study vaccine and one to receive the control saline) will have study product administered 24 hours before the remaining eighteen (18) participants. These two participants will be observed for at least 6 hours after study product administration to evaluate that no immediate serious adverse reactions have occurred, by measuring vital signs, change in the baseline symptoms and monitoring for occurrence of clinically significant symptoms and adverse events, The clinical investigator (CI) and the Independent Safety Monitor (ISM) will review all reactions including the solicited events that have occurred within the observation window for these two participants following study product administration and decide on whether the remaining participants will receive the first dose. If no immediate serious adverse reactions have been observed, the remaining participants will receive the first dose. The clinical and the adverse events recorded at the scheduled interim visits will be assessed by the SMC to assess the safety of the vaccine candidate prior to proceeding to the second dose.

Throat swabs will be taken from each participant at screening and on each day of study product administration. Rapid antigen test (QuickVue In-Line Strep A test) for group A streptococci will also be performed for each participant prior to each study product administration. Targeted physical examinations including cardiac auscultation by a physician will be performed on the day of each study product administration. Each participant will be observed for 30 minutes following administration of study product for evidence of immediate reactions.

A Memory Aid (MA) will be provided to participants to record their oral temperature, solicited and unsolicited symptoms, adverse events and concomitant medications. Each participant will be asked to record in memory aids the occurrence of any symptoms at the injection site (such as pain, tenderness, pruritis, erythema and induration) and systemic reactions such as fever, anorexia, nausea, malaise, myalgia, arthralgia and headache. Participants will also be asked to record any changes in urine that might suggest haematuria (blood-tinged or cola-coloured urine) and cutaneous abnormalities (rash or subcutaneous nodules). Information will be recorded daily for 7 days after each injection. Study personnel will review the information on the Memory Aid with the participant via phone calls (day 2 and 8 days after injection) to elicit as much information as possible about any reported symptoms. Based on this information, study staff will use his/her clinical judgment to assess the event and its severity and record the data on the Reactogenicity Record. Study staff will use the Reactogenicity Record to enter information into the database. The Memory Aid will not be collected from the participants.

All participants will be encouraged to contact clinical investigators or to visit the clinical site if they observe any grade 3 AE of the above mentioned reactions following each immunization.(see Appendix B), or if they have any concern. Adverse events and serious adverse events will also be reported at clinic visits throughout the study period.

Each participant will be required to visit the investigation site at the allocated days. Targeted physical examinations including cardiac auscultation by physician will be performed on day 28 after each vaccination and at follow-up visits on days 180, 266 and 350. Additional cardiac evaluation will include an electrocardiogram and transthoracic echocardiogram at day 28 following each injection and at the final follow-up visit on day 350. All study visits will be within the acceptable windows shown on Appendix A.

Biochemical and hematologic analyses for safety parameters including urinalysis will be performed for all participants at screening, prior to each injection and then at day 28 after each administered dose and at follow-up visits on days 180, 266 and 350. A urine pregnancy test will also be performed for all female participants on the day of each vaccination. Immunogenicity of the vaccine components will be determined by measuring the serum level of GAS peptide specific antibodies and cellular responses on each day of vaccination 28 days after each vaccination and at follow-up visits on days 180, 266 and 350. The induced level of GAS peptide antibodies will be used to monitor the kinetics of the antibody response after two vaccinations and to evaluate the response of subjects receiving the interventional vaccine compared to the placebo saline control. Moreover, serum sample of each participant at time points prior to each injection and at the final study visit on day 350 will be kept for use in testing for presence of human tissue cross-reactive antibodies should suitable assays for detection of cross reactive become available. The level of the anti-diphtheria toxoid antibodies in each participant will be measured prior to the each injection and at the end of the study. The expected duration of participant’s participation from screening to the final follow up visit will be approximately 13 months.

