| **Description of Study Design:** | The purpose of this study is to evaluate the safety and immunogenicity of a Group A Streptococcus vaccine candidate. The participants (N=20) will be randomized 3:1 to receive the active intervention (N=15) or saline as placebo control (N=5). Participants randomized for intervention will receive either 50 µg of the vaccine candidate or saline. 2 participants will be dosed, 1 placebo and 1 investigational product 24 hours before the remaining 18 participants. They will be observed for 6 hours for any immediate adverse events. The ISM will review the data prior to the other 18 participants receiving study product. If no immediate serious adverse reactions have been observed the other 18 participants will receive an intramuscular injection of 0.5mL volume of the assigned study product. Safety of the first dose will be assessed by the Safety Monitoring Committee (SMC) before proceeding to administering the second dose to all 20 participants on Day 56. Clinical and adverse events/serious adverse event assessment will be conducted throughout the study at the scheduled clinic visits. Clinical specimens (urine and blood) will be collected from each participant to assess the safety and the immunogenicity of the investigational vaccine. Echocardiograms and electrocardiograms will be performed throughout the study to assess the safety of the vaccine formulation. |
| **Estimated Time to Complete Enrollment:** | The enrollment of all participants in this study will take approximately 4 weeks. |

**Schematic of Study Design**: Screening, Study Product Administration, Safety Testing, Safety Monitoring Committee Review for the cohort of 20 subjects

| **Vaccine Trial Schedule** | |
| --- | --- |
| **Time** (day) |  |
| Day -28 to Day -7 | Screening  ECG/ECHO/hematology/chemistry/urinalysis/ASOT/-DNAse B |
| Day 0^ | Dose 1 (n = 15A*, 5C*) |
| Day 8±2 | Memory aid completion |
|  |  |
| Day 28±7 | ECG/ECHO/hematology/chemistry/urinalysis/ASOT/-DNAse B |
| Day 35±5 | Database Collection of Data (up to Day 28 data) |
|  |  |
| Day 49±5 | SMC Dose 1 review |
| Day 56±5 | Dose 2 (n = 15A*, 5C*) |
| Day 64±2 | Memory aid completion |
|  |  |
| Day 84±7 | ECG/ECHO/hematology/chemistry/urinalysis/ASOT/-DNaseB |
| Day 98±5 | Database Collection of Data (up to Day 84 data) |
|  |  |
| Day 126±7 | SMC Dose 2 review |
|  |  |
| Day 180±14 | Follow up visit  Hematology/chemistry/urinalysis/ASOT/-DNAse B |
|  |  |

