**Day 0, (Day of Dose 1)**

Two participants, one randomized to receive vaccine study product and the other control saline will have study product administered 24 hours prior to the remaining 18 participants which may be split into 2 cohorts. The safety of the first dose in these two participants will be initially observed for at least 6 hours and evaluated by the clinical investigator and the ISM to make recommendation on whether to proceed with administration of the study product to the remaining 18 participants.

These 2 participants will follow the events listed in Day 0 and will be dosed on Day 56 as all the participants of the study.

The safety of the first dose of the vaccine candidate in the study participants will be evaluated by a SMC that will make a recommendation to proceed to the administration of the next vaccine dose. See section 4 for the vaccine candidate dosage schedule. Refer to Appendix A for a tabular presentation of the study procedures.

Procedures to be followed at enrollment:

1. Review study eligibility and record concomitant medications.

2. Review medical history for any change in status from screening

3. Record baseline symptoms and vital signs. If the participant is febrile (temperature >38°C [>100.4F] or has an acute illness, the dose must be rescheduled. If rescheduled, the study product administration must be within 28 days after all screening procedures.

4. Targeted physical examination including cardiac auscultation. Particular attention to any elicited symptoms and signs consistent with rheumatic fever i.e. rash, arthalgia/arthritis (joint pain/swelling), renal angle tenderness and cardiovascular examination and movement disorder.

5. Obtain a throat swab and conduct a rapid antigen test for group A streptococci

6. Collect urine for urinalysis and blood for hematology, biochemistry and serology including, ASOT, α-DNase B, detection of α-J8 peptide vaccine specific antibodies, blood sample for quantitative cellular response as well as serum samples for α-DT antibodies and safety serum storage (refer to appendix D for tests required and blood volumes).

7. For female participants ensure that adequate contraceptive precautions have been taken since the screening pregnancy test and ensure that a urine test for -HCG is negative.

8. Perform breath alcohol test and urine drug screen.

9. Administer the study product.

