10. Observe the first two sentinels, the first two participants for at least 6 hours after study product administration to evaluate for any adverse reactions.

11. For all other participants, observe for at least 30 minutes after study product administration to evaluate for immediate adverse reactions.

12. Repeat vital signs after minimum of 30 minutes after study product administration or at least before discharge. Record any immediate injection site reaction or systemic reactions if they occur.

13. Educate the participant during the post-study product administration waiting period on proper use of the thermometers and injection site reaction measurement aid. Discuss the signs and symptoms of potential adverse events (AEs) and review the instructions on completion of the memory aid.

14. Distribute Day 0-7 Memory Aid (MA).

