**Day 2 ± 1 day (2 days after Dose 1, telephone call)**

1. Enquire for any acute complaints/adverse events/serious adverse events.

2. Review MA for solicited local and systemic reactogenicity and unsolicited events.

3. Review concomitant medications.

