• The injection site will be examined immediately before and after each dose. The reactogenicity of the study product will be determined by assessing the local pain, tenderness and pruritis and measuring the erythema/redness and induration/swelling at the injection site using the injection site reaction measurement tool (Appendix C).

• Solicited systemic symptoms (see section 9.2.1) will be assessed prior to study product administration and at 30 minutes after each dose. Memory aids will be given to each participant on each product administration day. All participants will be asked to record the occurrence of any injection site reaction or general symptoms for 7 days following each dose in memory aids as indicated in section 9.2.1. A telephone call will be made by a study nurse to each participant at 2 days and 8 days after each injection. All participants will be encouraged to call the clinical personnel involved in this study on the provided contact details, or to visit the clinical site if they observe any reactions, grade 3 or above as specified in this protocol (see Appendix B), or if they have any concern. Any AE that occurs greater than 7 days after each dose should be reported to the clinical study personnel during the scheduled interim visits or by calling the designated contact person. All AEs will be assessed during each study visit.

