## Safety Oversight (ISM plus SMC)

The Safety Oversight in this study will be under the direction of both Independent Safety Monitor (ISM) and the Safety Monitoring Committee (SMC).

Independent Safety Monitor

The ISM is a physician with relevant expertise, whose primary responsibility is to provide independent safety monitoring in a timely fashion. Participation is for the duration of the study and the ISM is appointed by the sponsor. The ISM should be able to access participant records readily in real time. The primary focus of the ISM is to independently review serious adverse events that may be associated with product and adverse events of special interest. The ISM should investigate those events considered serious and unexpected. Clinical and laboratory data, clinical records and other study-related records should be made available for ISM review. It is the responsibility of the CI to ensure that that the ISM is appraised of all new safety information relevant to the study product and the study. This includes providing the ISM with a copy of the Clinical Investigator’s Brochure (CIB) in advance, as well as promptly providing all CIB revisions and all other safety information issued by the sponsor that is received by the CI. The ISM should receive all protocol revisions and may receive other documents related to the study.

The ISM will be in communication with the CI at the enrollment site and the SMC chair for any event that needs further evaluation.

The ISM together with the clinical investigator (CI) will be also involved in the review of all reactions including the solicited events that have occurred within the observation window for the two participants that will initially receive the study product. The ISM will also be involved in the decision making by SMC on whether the remaining participants will receive the first dose.

The ISM will not be directly involved with the trial and is not under the CI’s supervision and has no financial, intellectual, proprietary or professional interest in outcome of the trial.

Safety Monitoring Committee

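### The go decision after the two sentinels need only use the first 6 hours or so, although the other 18 wait 24 hours; a required Day 1 call would close the gap cheaply

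*Protocol*

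**What the plan says.** Section 4 (Study Design) has two sentinels, one on vaccine and one on saline, dosed 24 hours ahead of the remaining 18. The aim given is to look for immediate serious reactions. The clinical investigator and the Independent Safety Monitor (ISM) "review all reactions including the solicited events that have occurred within the observation window for these two participants" and decide whether the others are dosed. Dosing goes ahead if no immediate serious reaction was seen.

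The length of that window is stated in several places:

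- Protocol Summary: "They will be observed for 6 hours for any immediate adverse events".
- Section 7.2, Day 0, with the investigator and the ISM as evaluators: "The safety of the first dose in these two participants will be initially observed for at least 6 hours and evaluated".
- Section 7.2, Day 0 procedures: "Observe the first two sentinels, the first two participants for at least 6 hours after study product administration".
- Section 9.6: the ISM's review again covers "solicited events that have occurred within the observation window for the two participants that will initially receive the study product".

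Each sentinel goes home with a memory aid for Days 0 to 7. Section 8.1 sets the first scheduled follow-up: "A telephone call will be made by a study nurse to each participant at 2 days and 8 days after each injection". Section 7.3 allows ± 1 day for the first of these calls, and Section 4 has the memory aid reviewed at these calls. Until then, participants are encouraged to make contact over a Grade 3 reaction, "or if they have any concern".

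**The concern.** The plan waits 24 hours but does not require the decision to use what could be known by then. From the end of observation until the 18 are dosed, the site learns of a sentinel's reaction only if the sentinel chooses to report it.

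The protocol itself treats this period as relevant to safety. Solicited reactions are collected for 7 days after each dose, and the Section 9.5 rules that halt product administration cover the same 7 days. Some of those rules are met by a single associated event, such as bronchospasm, another allergic event, or ulceration, abscess or necrosis at the injection site. No rule can act on an event that nobody has heard about.

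What is at stake is avoidable first-dose exposure. The Safety Monitoring Committee's approval before Dose 2 comes too late to protect anyone at Dose 1.

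**Working it through.** **Inputs from the protocol.** N = 20, randomized 3:1; 2 sentinels (1 vaccine, 1 saline); 24-hour lead; observation of at least 6 hours (Section 4 and Section 7.2); first call Day 2 ± 1 (Section 7.3).

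**Reproducing the plan's figures.** 20 × 3/4 = 15 vaccine and 20 × 1/4 = 5 saline. After the sentinels, 20 − 2 = 18 remain: 15 − 1 = 14 vaccine and 5 − 1 = 4 saline. These agree with the protocol.

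**The gap.**

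- Hours with no required ascertainment before the 18 are dosed: 24 − 6 = up to 18, or 18/24 = 75% of the interval.
- First scheduled call: nominally 48 hours after the sentinels' dose, with an allowed range of about 24 to 72 hours. That is nominally 48 − 24 = 24 hours, and at most about 72 − 24 = 48 hours, after the others are dosed.
- Further people who may have had vaccine by then: up to 14. The number could be lower if the 18 are split into two cohorts, which Section 7.2 permits.

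**How often a Day 1 call would matter.** The protocol gives no reaction rates, so two quantities are assumed:

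- p = rate of associated Grade 3 reactions in vaccine recipients: 5%, 10% or 20%.
- q = share of such reactions that both start in hours 6 to 24 and are not self-reported: 10% to 50%.

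Only one sentinel receives vaccine, so the chance that a Day 1 call finds a reaction the plan would miss is p × q. If that finding stopped dosing for good, the expected number of Grade 3 reactions avoided among the other 14 would be (p × q) × 14p, taking reactions as independent.

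| p | p × q (q = 10% to 50%) | 14p | Reactions avoided, (p × q) × 14p |
|---|---|---|---|
| 5% | 0.5% to 2.5% | 0.7 | 0.004 to 0.018 |
| 10% | 1% to 5% | 1.4 | 0.014 to 0.07 |
| 20% | 2% to 10% | 2.8 | 0.056 to 0.28 |

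The last column is an upper figure for each pair of assumptions, because Section 9.5 provides for a halt and review, not an automatic permanent stop.

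**The case against.** The strongest reply is that the step does what it was set up to do. Its aim is to detect immediate serious reactions, and at least 6 hours of observation with review by the investigator and the ISM serves that aim. This stands: a reader might infer that the plan contradicts itself or chose a wrong window, and the text supports neither.

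Existing safeguards also count. Six hours is a minimum. The Summary has the ISM review data before the 18 are dosed, without stating a cut-off. Section 9.6 gives the ISM ready access to records and has the investigator pass on new safety information. The first call may fall on Day 1. Participants are taught to measure temperature and local reactions, and a Grade 3 reaction (for example fever of 39 °C or more, or redness over 10 cm) is hard to overlook. A q near 50% is therefore generous: it would need, say, every Grade 3 reaction to begin in hours 6 to 24 and half of them to go unreported. These points make a miss less likely, but none requires anyone to ask the sentinels before the 18 are dosed.

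A third reply is that the go criterion concerns serious reactions, so a non-serious Grade 3 fever would not by itself fail it even at hour 3. That is correct. A call alone improves what is known; a hold for Grade 3 reactions is an additional criterion and should be presented as one.

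A reader might also infer that the gap causes the reactions that would occur among the other 14. It does not: in most trials they would occur whether or not a call was made. Nor should the point rest on the 10% halting thresholds being diluted as more people are dosed. That depends on whether those enrolled to date number 2 or 20 at the sentinel step, and Sections 5 and 11.4 can be read either way.

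**Conclusion.** The point holds as a cheap safety improvement, not as an error in the plan. The required go review covers a minimum of 6 of the 24 hours, and the visit text requires no sentinel contact or memory-aid review before the 18 are dosed. An associated reaction in hours 6 to 24 that is not self-reported could therefore be learned of only after up to 14 further people have had vaccine.

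The expected benefit is small. With p = 5% to 20% and q = 10% to 50%, both assumed, the call finds something new with a chance of about 0.5% to 10%. It avoids about 0.004 to 0.28 Grade 3 reactions on average, if a hold became a permanent stop. The change is still worth making because it costs so little and the 24-hour wait is already in the schedule.

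The conclusion rests on the visit text. Appendix A, the committee charter and the site work instructions were not available; if they already require a Day 1 contact before dosing, only an aligning sentence in the protocol is needed.

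**What to change.** 1. Schedule the sentinels' first telephone call on Day 1, before any of the 18 are dosed, or add a call then and keep the Day 2 ± 1 call. Document it, and cover memory-aid entries up to that time.
2. Include these data in the review by the clinical investigator and the ISM.
3. Have them hold dosing for review if either sentinel has a study-product-associated reaction of Grade 3 or higher, or meets any Section 9.5 rule that a single event triggers. Say openly that the Grade 3 hold is added to the present criterion of no immediate serious reaction.
4. Align the Protocol Summary and Sections 4, 7.2 and 9.6 to this data cut.

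The cost is at most two extra short calls and a line in each of those places, with no new staff and no change to sample size or dosing schedule. The downsides are that the ISM must confirm on the morning of dosing and, if the call is additional, that the sentinels have one more contact than the other 18.
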